### 9.4.4 Safety Analyses

All safety summaries and analyses will be made on the safety analysis set.

AEs will be coded with Medical Dictionary for Regulatory Activities (MedDRA).

AEs will be summarised by study part and treatment group, below incidences will be provided for the 28-day follow-up period:

- Proportion of subjects with any AEs
- Proportion of subjects with any AEs by system organ class (SOC) and preferred term (PT)
- Proportion of subjects with any AEs by SOC and PT and worst toxicity grade
- Proportion of subjects with Grade  $\geq 3$  AEs
- Proportion of subjects with Grade  $\geq 3$  AEs by SOC and PT

- Proportion of subjects with serious AEs (SAEs)
- Proportion of subjects with SAEs by SOC and PT
- Proportion of subjects with SAEs by SOC and PT and worst toxicity grade
- Proportion of subjects with SUSARs
- Proportion of subjects with treatment-related AEs
- Proportion of subjects with treatment-related AEs by SOC and PT
- Proportion of subjects with treatment-related AEs by SOC and PT and worst toxicity grade
- Proportion of subjects with treatment-related Grade  $\geq 3$  AEs
- Proportion of subjects with treatment-related Grade  $\geq 3$  AEs by SOC and PT
- Proportion of subjects with any AEs leading to discontinuation
- Proportion of subjects with any AEs leading to hospitalisation
- Proportion of subjects with treatment-related SAEs
- Proportion of subjects with treatment-related SAEs by SOC and PT
- Proportion of subjects with treatment-related SAEs by SOC and PT and worst toxicity grade
- Proportion of subjects with IRR (i.e., within 24 hours of start of infusion)
- Proportion of subjects with hypersensitivity reactions (other than those reported as IRRs) within 28-day FU period

Observed values of clinical safety laboratory parameters and vital signs will be summarised by study part, treatment group and by timepoints using descriptive statistics. Shift tables for change from baseline will be provided.

Shift table for changes from baseline in 12-lead ECGs (i.e., shifting from a normal to an abnormal clinical assessment or vice versa) will be presented as well.

#### 9.4.5 Pharmacokinetic Analyses

Pharmacokinetic analyses will be performed by Parexel on behalf of ExeVir Bio BV using non-compartmental analysis.

When possible, the following PK parameters will be assessed for XVR011:

- $C_{\max}$ : maximum observed plasma concentration
- AUC: area under the plasma concentration-time curve
- $t_{1/2}$ : apparent plasma terminal elimination half-life

XVR011 plasma concentrations and PK parameters will be listed and summarised by XVR011 treatment groups and study parts.

#### **9.4.6 Other Analyses**

Levels of ADAs and nAbs will be reported as continuous endpoints.

Biomarker exploratory analyses will be described in the SAP.

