- Oxygen supplementation details (duration and type), respiratory rate, oxygen saturation on room air and with oxygen supplementation.
- Study treatment administration within 12 hours of randomisation and under medical supervision for the whole duration of the infusion and for two hours after the end of the infusion.
- Symptom- or history-directed examination.
- The Investigator will make an assessment of intensity for each AE and SAE reported during the study, according to National Cancer Institute Common Terminology Criteria for Adverse Events (NCI-CTCAE) version 5.0.
- Women of childbearing potential (Appendix 5) will have a urine pregnancy test. If found positive, will have a serum pregnancy test.
- If applicable in the judgement of the Investigator, menopausal status should be confirmed by a FSH level in the post-menopausal range, particularly in post-menopausal women who are not using hormonal contraception or hormonal replacement therapy.
- The Investigator or designee will perform signs and symptom assessment using the Food and Drug Administration (FDA) sign and symptoms scoring system (assessment of 14 common COVID-19-Related Symptoms).
- The PK samples will be collected within 60 minutes pre-dose, 30 ± 15 minutes post-dose (from the end of infusion) on Day 1, 72 ± 2 hours post-dose on Day 4, on Day 8, on Day 15, Day 29, Day 60 and on Day 90. Samples are also taken at ED.
- Day 1 (baseline) safety laboratory parameters do not need to be repeated if the corresponding screening laboratory parameters have been done within 24 hours of the start of treatment.
- These assessments only need to be performed if the ED takes place during the Endpoint Assessment Period.

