| To evaluate the pharmacokinetics (PK) of XVR011, following a single intravenous infusion in subjects hospitalised for COVID-19                   | 
 
Blood concentrations of XVR011 and PK parameters (<math>C_{max}</math>, AUC, <math>t_{1/2}</math>) on Days 1, 2, 4, 8, 15 and Day 29.
 
                                                                                                                                                                                       |
| To evaluate the immunogenicity of XVR011, following a single intravenous infusion in subjects hospitalised for COVID-19                          | 
 
ADAs and nAbs at baseline (Day 1 pre-dose), Day 15, and Day 29
 
                                                                                                                                                                                                                                                              |

ADA = anti-drug antibody; AE = adverse event; AUC = area under the plasma concentration-time curve;  $C_{max}$  = maximum observed plasma concentration; COVID-2019= coronavirus disease 2019; CRP = C-reactive protein; FU = follow-up; ICU = intensive care unit; LDH = lactate dehydrogenase; nAb = neutralising anti-drug antibody; RT-qPCR = reverse transcriptase quantitative polymerase chain reaction;  $t_{1/2}$  = apparent plasma terminal elimination half-life.

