| To determine the PK parameters of XVR011, following a single intravenous infusion in subjects hospitalised for COVID-19                          | 
 
Blood concentrations of XVR011 and PK parameters (<math>C_{max}</math>, AUC, <math>t_{1/2}</math>) on Days 1, 4, 8, 15, 29, 60 and 90.
 
                                                                                                                                                                                                                                                                                |
| To evaluate the immunogenicity of XVR011, following a single intravenous infusion in subjects hospitalised for COVID-19, compared to placebo     | 
 
ADAs and nAbs at baseline (Day 1 pre-dose), Day 15 and Day 29.
 
                                                                                                                                                                                                                                                                                                                                                        |

a Any form of mechanical ventilation includes but not limited to high flow oxygen therapy, continuous positive airway pressure, invasive mechanical ventilation

ADA = anti-drug antibody; AE = adverse event; AUC = area under the plasma concentration-time curve;  $C_{max}$  = maximum observed plasma concentration; COVID-2019= coronavirus disease 2019; CRP = C-reactive protein; FU = follow-up; ICU = intensive care unit; LDH = lactate dehydrogenase; nAb = neutralising anti-drug antibody; RT-qPCR = reverse transcriptase quantitative polymerase chain reaction;  $t_{1/2}$  = apparent plasma terminal elimination half-life.

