## **8.5 Pharmacokinetics**

Serum samples of approximately 1 mL will be collected for measurement of serum concentrations of XVR011 as specified in the SoA. The timing of sampling may be altered during the course of the study based on newly available data (e.g., to obtain data closer to the time of peak plasma concentrations) to ensure appropriate monitoring. Instructions for the collection and handling of biological samples will be provided in a separate laboratory manual. The actual date and time (24-hour clock time) of each sample will be recorded.

Samples will be used to evaluate the PK of XVR011 and processed as described in the laboratory manual. Genetic analyses will not be performed on these samples. Subject confidentiality will be maintained.

During Part 2, drug concentration information that would unblind the study will not be reported to investigative sites or blinded personnel until the study has been unblinded.

Any changes in the timing of timepoints for any planned study assessments must be documented and approved by the relevant study team member and then archived in the Sponsor and site study files but will not constitute a protocol amendment. The IRB/IEC will be informed of any safety issues that require alteration of the safety monitoring scheme or amendment of the ICF.

Samples may be stored for a maximum of 5 years following the last subject's last visit for the study at a facility selected by the Sponsor to enable further analysis of immune responses to XVR011.

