## 8.9 Immunogenicity Assessments

Antibodies to XVR011 will be evaluated in serum samples collected from all subjects, according to the SoA.

Serum samples will be screened for antibodies binding to XVR011 and the titre of confirmed positive samples will be reported. Other analyses may be performed to verify the stability of antibodies to XVR011 and/or further characterise the immunogenicity of XVR011.

The detection and characterisation of antibodies to XVR011 will be performed using a validated assay method by or under the supervision of the Sponsor. Additional samples may be collected to

further characterised and/or evaluated antibodies for their ability to neutralise the activity of the study treatment. For more details see laboratory manual.

Instructions for the collection and handling of biological samples will be provided in a separate laboratory manual.

Samples may be stored for a maximum of 3 years following the last subject's last visit for the study at a facility selected by the Sponsor to enable further analysis of immune responses to XVR011.

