### **9.4.1 General Considerations**

All statistical analyses will be performed by Parexel. All statistical analysis will be performed using the latest available version of SAS® (SAS Institute Inc., Cary, North Carolina, United States of America [USA]), version 9.2 or higher.

Continuous data will be summarised by treatment group using descriptive statistics (number, mean, median, standard deviation [SD], minimum, and maximum). Categorical data will be summarised by treatment group using frequency tables (frequency and percent).

Unless other way specified, baseline will be taken as the last available assessment prior to dosing on Day 1.

All statistical tests will be 2-sided and will be performed at the 5% level of significance, thus 95% confidence intervals (CIs) will be computed, unless otherwise stated.

A protocol deviation is defined as any change, divergence, or departure from the study design or procedures of a study protocol. Protocol deviations can lead to the exclusion of a subject from the PPS. Protocol deviations will be reviewed and classified at the Blinded Data Review Meeting (BDRM) prior to unblinding; the exclusion of subjects from PPS will be decided at BDRM.

Unless otherwise stated, missing data will not be imputed.

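### Section 9.4.6 summarises ADA and nAb as continuous levels although titres exist only for confirmed positives; it should report how often each arm responds and tie the Part 2 conclusion to Day 29

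*Protocol*

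**What the plan says.** **Analysis.** Section 9.4.6 gives one sentence on immunogenicity: "Levels of ADAs and nAbs will be reported as continuous endpoints". The sentence after it leaves the biomarker analyses to the SAP, but the ADA and nAb sentence contains no such deferral.

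**What the assay produces.** Section 8.9 states: "Serum samples will be screened for antibodies binding to XVR011 and the titre of confirmed positive samples will be reported". It describes no level for a negative sample. For nAbs, it mentions testing whether antibodies neutralise the drug but names no quantitative readout.

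**How continuous data are summarised.** Section 9.4.1 gives continuous data the number, mean, median, SD, minimum and maximum by treatment group, and keeps frequency tables for categorical data. It adds: "Unless otherwise stated, missing data will not be imputed".

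**Timing.** Table 3–1 (Part 1) lists "ADAs and nAbs at baseline (Day 1 pre-dose), Day 15, and Day 29" and Table 3–2 (Part 2) lists "ADAs and nAbs at baseline (Day 1 pre-dose), Day 15 and Day 29". The Part 2 objective is a comparison with placebo. At early discontinuation in Part 2, a footnote to Table 1–2 limits the ADA/nAb sample: "These assessments only need to be performed if the ED takes place during the Endpoint Assessment Period". PK blood in Part 2 continues "on Day 8, on Day 15, Day 29, Day 60 and on Day 90". Section 8.5 allows PK samples to be stored for up to 5 years "to enable further analysis of immune responses to XVR011".

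**The concern.** A tiered ADA assay answers two questions: how many subjects respond, and how strongly the responders respond. Section 9.4.6 names a summary for the second question only, while the Part 2 objective needs the first, arm against arm. Comparing titres among positives conditions on something that happens after randomisation. Two arms with the same titres among responders would look alike however different their response rates.

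The way round this, giving negatives a number so that everyone has a level, makes the mean and SD depend on the number chosen, and the protocol gives none.

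The second part concerns time. In Part 2 the drug is followed to Day 90 but scheduled immunogenicity testing ends at Day 29, when a substantial share of a long-lived antibody is expected to remain. A response first appearing later lies outside the scheduled tests, so an unqualified statement on immunogenicity would claim more than was examined.

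**Working it through.** The protocol states no figure on this point, so there is none to reproduce.

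**Step 1. Read the three sections together.** Section 8.9 gives a titre to confirmed positives only, Section 9.4.1 leaves missing values missing, and Section 9.4.6 asks for a continuous summary. There are two possible outcomes:
- Negatives carry no value, and the mean and SD describe positives alone.
- Negatives receive a value that the protocol does not define.

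Neither is a comparison of response frequency.

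**Step 2. How many subjects would carry a titre.** Arm sizes come from Section 9.2 (272 XVR011, 136 placebo). Incidence is not given, so 5%, 10% and 20% are assumed. Count = arm size × incidence.

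| Assumed incidence | XVR011 with a titre | Placebo with a titre | Share without a titre |
|---|---|---|---|
| 5% | 272 × 0.05 ≈ 14 | 136 × 0.05 ≈ 7 | 95% |
| 10% | 272 × 0.10 ≈ 27 | 136 × 0.10 ≈ 14 | 90% |
| 20% | 272 × 0.20 ≈ 54 | 136 × 0.20 ≈ 27 | 80% |

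Suppose 54 of 272 respond on XVR011 (20%) and 7 of 136 on placebo (5%), with the same titre distribution among responders. The expected difference in mean titre is zero, although the response rates differ fourfold.

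**Step 3. What a proportion would give.** With exact (Clopper–Pearson) 95% intervals on n = 272, 27 positives (9.9%) give 6.6% to 14.1%, and 0 positives give an upper limit of 1.3%. The planned samples support a usable estimate of incidence to Day 29.

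**Step 4. Drug remaining at the sampling days.** Fraction = 0.5^((day − 1)/t½), assuming mono-exponential decay. Two half-lives are used:
- 21 days, the design aim in Section 2.1, not a measured value.
- 14 days, implied by Section 4.3. Doubling the dose from 500 to 1000 mg extends the projected time above 50 µg/mL from 7 to 21 days. Under dose proportionality one doubling buys one half-life, so 21 − 7 = 14 days.

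| Day | t½ = 21 days | t½ = 14 days |
|---|---|---|
| 15 | 63.0% | 50.0% |
| 29 | 39.7% | 25.0% |
| 60 | 14.3% | 5.4% |
| 90 | 5.3% | 1.2% |

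Five half-lives are 70 to 105 days.

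**Step 5. Projected concentration at Day 29.** Carry the Section 4.3 thresholds forward: C = threshold × 0.5^((28 − time above threshold)/t½).
- 250 mg: 27 × 0.5^(21/t½) = 9.5 to 13.5 µg/mL
- 500 mg: 50 × 0.5^(21/t½) = 17.7 to 25.0 µg/mL
- 1000 mg: 50 × 0.5^(7/t½) = 35.4 to 39.7 µg/mL

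Any of the three doses could be used in Part 2. These figures show drug present at the last scheduled ADA sample. They do not show missed antibodies.

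**The case against.** The strongest reply is that nothing is lost. Section 8.9 has all subjects' samples screened, at baseline, Day 15 and Day 29, with a concurrent placebo arm. Positive status and treatment-emergent response by Day 29 can therefore be counted, and a SAP could tabulate them. This stands, and it rules out a conclusion a reader might draw: that the trial could not estimate ADA incidence. The fault lies in the summary that the protocol names, not in the data.

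The literal plan would also print a count, because the number of observations belongs to the continuous summary. If negatives carry no value, that number is the positives per arm and visit. This holds in part. It supplies a numerator without the number tested, without a split by baseline status and without a comparison, and it disappears if negatives are given a value.

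It can be said that such detail belongs in the SAP, which is not at hand. That would be right if Section 9.4.6 were silent or deferred the matter. Instead it fixes a type of summary that does not match the assay output.

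On timing, the objectives table and the schedule agree on Day 29, so there is no contradiction between them. A reader might infer that later responses could never be seen. The documents do not support that: Section 8.5 allows stored PK serum to be used for immune-response work, and Section 8.9 allows additional samples. These provisions are permissive, however; no Day 60 or Day 90 test is scheduled.

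A reader might also infer that residual drug will hide antibodies. That depends on the assay's drug tolerance, which the protocol does not state.

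**Conclusion.** The point holds in a limited form. Section 9.4.6 names a continuous summary for a result that is positive or negative, with a titre among positives only. As written, it does not deliver the comparison with placebo that the Part 2 objective asks for. At an assumed incidence of 5% to 20%, between 80% and 95% of subjects would contribute no titre.

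Scheduled ADA/nAb testing in Part 2 supports conclusions to Day 29 only. About 25% to 40% of drug would remain then, assuming mono-exponential decay and a half-life of 14 to 21 days. Masking by that drug is possible but not demonstrated.

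The consequence is small. The endpoint is exploratory, and the primary analysis and sample size are untouched.

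**What to change.** 1. Replace the ADA/nAb sentence in Section 9.4.6. Report the number tested and the number and percentage ADA-positive and nAb-positive, by arm and visit. Split them into baseline-positive and treatment-emergent, with boosted responses included in the latter. Summarise titres among positives on the log scale. This costs nothing beyond the edit, because the results are already collected.

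2. For Part 2, choose one of two courses:
   - State that the immunogenicity conclusion applies to Day 29 only. This is free.
   - Optionally, run the ADA/nAb assay on the serum already drawn for PK at Days 60 and 90. By Day 90, about 1% to 5% of drug would remain under the same assumptions. This costs assays but no new visit or blood draw. PK samples are about 1 mL (Section 8.5), so check first that enough volume is left.

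In Part 1, Day 29 is the end of study, so only the first change applies.

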#### **9.5 Interim Analyses**

An interim analysis will be conducted when all subjects enrolled in Part 1 have completed the Day 4 visit, including all available safety, tolerability, preliminary efficacy, PK and PD data.

The SAP will describe the planned interim analyses in greater detail.

#### **9.6 Data Monitoring Committee**

An IDMC will review data and provide recommendations during the study. For details on the IDMC, refer to Appendix 10.1.5.

## **10 Supporting Documentation and Operational Considerations**

### **10.1 Appendix 1: Regulatory, Ethical, and Study Oversight Considerations**

#### **10.1.1 Regulatory and Ethical Considerations**

This study will be conducted in accordance with the protocol and with:

- Consensus ethical principles derived from international guidelines, including the Declaration of Helsinki and Council for International Organisations of Medical Sciences (CIOMS) International Ethical Guidelines.
- Applicable ICH Good Clinical Practice (GCP) Guidelines.
- Applicable laws and regulations.

The protocol, protocol amendments, ICF, Investigator Brochure, and other relevant documents (e.g., advertisements) must be submitted to an IRB/IEC by the Investigator and reviewed and approved by the IRB/IEC before the study is initiated.

Any amendments to the protocol will require IEC/IRB approval before implementation of changes made to the study design, except for changes necessary to eliminate an immediate hazard to study subjects.

The Investigator will be responsible for the following:

- Providing written summaries of the status of the study to the IRB/IEC annually or more frequently in accordance with the requirements, policies, and procedures established by the IRB/IEC.
- Notifying the IRB/IEC of SAE or other significant safety findings as required by IRB/IEC procedures.
- Overall conduct of the study at the site and adherence to requirements of 21 CFR, ICH GCP guidelines, the IRB/IEC, European regulation 536/2014 for clinical studies (if applicable), and all other applicable local regulations.

#### **10.1.2 Financial Disclosure**

Investigators and sub-Investigators will provide the Sponsor with sufficient, accurate financial information in accordance with local regulations to allow the Sponsor to submit a complete and accurate financial certification or disclosure statements to the appropriate regulatory authorities. Investigators are responsible for providing information on financial interests during the course of the study and for 1 year after completion of the study.

### **10.1.3 Informed Consent Process**

The Investigator or his/her representative will explain the nature of the study to the subject or his/her legally authorised representative and answer all questions regarding the study.

Subjects must be informed that their participation is voluntary. Subjects or their legally authorised representative will be required to sign a statement of informed consent that meets the requirements of 21 CFR 50, local regulations, ICH guidelines, Health Insurance Portability and Accountability Act (HIPAA) requirements, where applicable, and the IRB/IEC or study site.

The medical record must include a statement that written informed consent was obtained before the subject was enrolled in the study and the date the written consent was obtained. The authorised person obtaining the informed consent must also sign the ICF. If due to COVID-19 restrictions written consent is not possible, verbal informed consent in the presence of an impartial witness will be obtained and documented in the medical record.

Subjects must be re-consented to the most current version of the ICF(s) during their participation in the study.

A copy of the ICF(s) must be provided to the subject or the subject's legally authorised representative.

If a protocol amendment is required, the ICF may need to be revised to reflect the changes to the protocol. If the ICF is revised, it must be reviewed and approved by the appropriate IEC/IRB and signed by all subjects subsequently enrolled in the study as well as those currently enrolled in the study.

